### Detailed Study Procedures

#### Recruitment and Screening

Youth participants will be recruited from community groups, after-school and extracurricular programs, parent organizations, private psychiatric and pediatric primary care clinics, and religious organizations in the Stony Brook area. Eligibility for participation will be ascertained through a parent phone screen conducted by a trained member of the research team. Parents will be informed at the end of the phone screen whether or not their adolescent qualifies for study participation. Youths must be living with at least 1 parent or legal guardian and both must speak English well enough to complete study interventions. Additional inclusion criteria will include the following: (1) the youth is aged 12 to 16 years (inclusive) with 1 parent willing to participate (2) the youth reports elevated depressive symptoms (>80 percentile for age and sex, reflecting subclinical or higher symptom elevations) based on the parent-report version of the Children’s Depression Inventory-2 (CDI-2). Exclusion criteria will include intellectual disability (based on parent report) and hospitalization of the adolescent within the past 2 months for suicide attempt or self-harm, as the interventions being evaluated in this study are not designed for youth with acute medical or psychiatric need. Concurrent treatment will not preclude eligibility. Youths prone to seizures will also be eligible to participate; risks of participating will be discussed with prospective participants and families before study participation. This study will focus on youth aged 12 to 16 years because depression increases markedly in adolescence, and youth in this age range have responded well to GMI [13,14].

#### Laboratory-Based Study Session

On the basis of the parent phone screen, parents of eligible youths will be invited to schedule a laboratory-based study session, which they and their adolescent will attend together. This session will last approximately 2 hours and will be led by 2 research assistants at the postbaccalaureate, master’s, or advanced undergraduate level. Before guiding participants through the study, each research assistant will have received individual training from the principal investigator in each step of the study protocol, including 2 start-to-finish *practice runs* with mock participants.

At the start of this laboratory-based study session, the youth and parent will have the opportunity to provide consent or parental permission and youth assent; all study procedures will be explained to the family at this time, and the youth and parent will be reminded that they can choose to leave the study at any time. After providing parental permission and youth assent, study procedures will begin. The youth participant will be escorted to a separate room by a member of the study team to complete study procedures; the parent will remain in the room in which consent and assent was obtained to complete his or her portion of the study procedures (ie, a questionnaire battery). One member of the study team will remain with the youth for the duration of the session; a second member of the study team will provide instructions to the parent and remain available to answer any additional questions the parent has during the laboratory visit.

After consenting, youths will be asked to complete a battery of questionnaires (detailed below) via Qualtrics, a secure collection platform. Subsequently, a random number generator (embedded within the last slide of the Qualtrics survey including youths’ baseline questionnaires) will be used to assign youths to one of 3 intervention conditions: VR GMI, Web-based GMI, or Web-based ST. No personally identifying data or information will be collected during intervention administration.

Notably, for youths randomly assigned to the VR GMI, both the youth and experimenter will be aware of the condition assignment (only one of the 3 programs involves VR technology). However, for youths randomly assigned to either of the 2 Web-based interventions neither the youth nor the experimenter will be aware of which Web-based intervention they received; randomization to these 2 conditions will occur without experimenter involvement as part of the youth’s Qualtrics survey.

### Interventions

#### Web-Based Growth Mindset Intervention

The Web-based GMI [13,14], called Project Personality, is delivered via Qualtrics and takes approximately 30 min to complete. All intervention activities are self-administered by the youth and delivered in a Web-based format, including illustrations and audio-recordings of text. Intervention content is designed to maximize relevance for youths experiencing symptoms of depression, including excessive sadness and hopelessness. The intervention includes 5 components: (1) an introduction to the brain, including a lesson on the concept of neuroplasticity, describing how and why our behaviors are controlled by thoughts and feelings in their brains, which have potential for change; (2) written testimonials from older youths who describe their beliefs that people’s personal traits (eg, sadness and anxiety) are malleable, given the brain’s plasticity; (3) additional vignettes written by older youths, describing times when they used *GMs* to persevere through social and emotional setbacks; (4) a summary of scientific studies suggesting that personality can, and often does, change in positive ways over time; and (5) exercises in which the participants write notes to peers, drawing on scientific information to describe the malleability of people’s personal traits.

#### Virtual Reality Growth Mindset Intervention

The VR intervention, called the VR Personality Project, will be administered through an adjustable VR headset that includes a stereoscopic display powered by a Samsung smartphone (Galaxy S6TM) mounted on a lightweight (345 g) wireless, off-the-shelf head-mounted display with a 101-degree field of view for users (Samsung Gear Virtual Reality (VR)™). A focus wheel on the VR goggles will be adjusted to find a comfortable focal length for each participant. Sound is delivered through the head-mounted display. A lightweight (295 g) wireless Bluetooth controller (MOGA PROTM POWER controller) that requires only one hand to operate will be used by each adolescent to interact with the VR environment. For infection control reasons and because the same hardware will be used for all participants, disposable coverings will be used on the head-mounted display. All equipment will be cleaned between participants using disposable wipes and dried for at least 20 min.

Similar to the Web-based analogue, the VR Personality Project takes approximately 30 min for youths to complete. It contains each of the components included in the Web-based GMI, including a lesson on neuroplasticity (Figure 1); testimonials from older peers; information about research suggesting the malleability of personal traits (Figure 2); and a self-persuasion exercise wherein the participant provides advice to a student in the VR environment who has just experienced a peer-related setback. Content is delivered by *characters* in the VR environment (adolescent and adult actors hired and filmed for the creation of this intervention), who are matched to an adolescent’s self-identified gender identity for a more personalized experience (Figure 3). These characters help guide the youth participant through each stage of the program, providing scientific information and personal stories. The primary difference between the VR and Web-based GMI involves the content delivery system and, by extension, the level of immersion each intervention offers. The VR program is designed to be immersive, fun, and interactive; the youth have an opportunity to choose to speak to various scientists and students within the VR environment and can navigate from one scene to the next; by contrast, in the online program, participants are automatically exposed to a series of text-based activities. Additionally, the VR Personality Projects provides participants the opportunity to provide advice (by speaking aloud to a student) in the VR environment, immediately after the student experiences a setback. Thus, the intervention offers a more self-directed, active experience for participants, as opposed to the passive experience of progressing through a largely text-based online program. Distinctions and similarities in user experience and content between the Web-based and VR GMIs are outlined in Table 1.

Youths who become dizzy or experience discomfort during the VR experience will be permitted to take breaks, or stop participating, at any time. Generally, glasses fit within the VR headset and may be worn during the intervention; however, the choice to wear or remove glasses (for participants who wear them) will be made on a person-to-person basis, based on personal preference and comfort. Youths will be reminded of this at the start of the laboratory session and again before starting the VR experience for those randomized to this condition.

**Figure 1 figure1:**
[figure not shown]
Screen Capture from VR Personality Project – lesson on neuroplasticity.

**Figure 2 figure2:**
[figure not shown]
Screen Capture from VR Personality Project – a “scientist” describes research suggesting the malleability of personal traits.

**Figure 3 figure3:**
[figure not shown]
Screen Capture from VR Personality Project. 3a: Participants select gender identity. 3b: Peer guides for adolescents who are male-identifying. 3c: Peer guides for adolescents who are female-identifying. Adolescents who select “another identity” or “rather not say” encounter peer guides shown in panel 3b.

**Table 1 table1:** Similarities and differences between the virtual reality (VR) and computer-based personality project interventions.

Intervention design feature	Virtual reality personality project	Computer-based personality project
Delivery format	Immersive, 360-degree virtual reality environments	Computer-based program delivered via Qualtrics survey
Personalization of intervention content	Characters in program vary in age, gender identity by participant-selected age and gender identity	Static program content; no personalization by user characteristics
Degree of user choice	Participants select when to proceed to subsequent intervention sections; where to focus attention and which characters to speak to in a variety 360-degree environment; how many questions to ask program *characters*; and whether to engage in each intervention activity	Participants select when to proceed to subsequent intervention sections and whether listen to audio-recordings of written intervention text
Core program content	Lesson on neuroplasticity and the brain; psychoeducation regarding links between thoughts, feelings, and actions; peer and scientist testimonials, “saying-is-believing” activities to solidify learning. Delivered by characters and computerized animations in various VR environments.	Lesson on neuroplasticity and the brain; psychoeducation regarding links between thoughts, feelings, and actions; peer and scientist testimonials, “saying-is-believing” activities to solidify learning. Delivered via written text and accompanying audio-recordings of text.
Structure of “saying-is-believing” activity	Participants witness a program character undergo an in-vivo stressor related to depressive symptoms. Participants (a) describe how they themselves would feel, were they to experience a similar stressor, by speaking out-loud to the VR program guide, and (b) offer advice to help this character cope more effectively with the setback, again by speaking out-loud to the program character. Participants select when to begin and stop speaking.	Participants read about a peer undergoing a stressor related to depressive symptoms. Participants (a) write about how they themselves would feel, were they to experience a similar stressor, and (b) offer written advice to help this peer cope more effectively with the setback (using newly-gleaned knowledge about personality and the brain).

#### Web-Based Supportive Therapy

The Web-based ST [13,14] intervention, called the Sharing Feelings Program, is delivered entirely via Qualtrics, is self-administered by youths, and takes approximately 30 min to complete. It is structurally similar to the Web-based GMI, but it is designed to mimic ST. The goals of the ST intervention are to encourage youths to identify and express feelings to close others; the intervention does not teach or emphasize specific skills or beliefs. In a previous trial, ST led to smaller improvements in adolescent stress recovery, perceived control, and internalizing problems compared with a GM program [13,14]. The ST SSI is designed to control for nonspecific aspects of intervention, including engagement in a computer program. It includes the same number of reading and writing activities as the Web-based mindset intervention; it also mirrors the Web-based mindset intervention’s structure, including vignettes written by older peers describing times when they benefited from sharing feelings with close others. Immediately following intervention completion, all youths (regardless of condition assignment) will be asked to complete the same battery of questionnaires immediately postintervention to index immediate shifts in proximal outcomes.

After both the youth and the parent have completed their respective portions of the study, the laboratory visit will conclude. All study participants will be offered referral information for psychotherapy and/or pharmacologic treatment at Stony Brook and the surrounding community. Participants will not be excluded from completing study procedures if they begin receiving treatment for psychological distress during the study.

Before the youth and parent leave the laboratory, study personnel will inspect the youth and parent questionnaire responses on items inquiring about suicidal ideation. If there is any indication of adolescent suicidal ideation during the laboratory session, risk assessments will be conducted by trained study personnel. In the event that a participant is in imminent danger to themselves or others, their accompanying parent will be informed. Study personnel will meet with the family to establish a safety plan. In the event of reported, active suicidal ideation or plan, the family will be accompanied to the Psychiatric Emergency Program at the nearby University Hospital.

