### Aim 3: Test Mediation Through Perceived Control

To test whether the VR intervention and the Web-based GM intervention reduces youth-reported depressive symptoms through proximal increases in perceived control, we will conduct multiple mediation analyses which involve simultaneous indirect effects by multiple variables [44]. This approach allows for both an analysis of the total indirect effect (the aggregate indirect effect of all the candidate mediators under investigation) and analyses of specific indirect effects (ie, of each mediator under investigation). For mediation models assessing perceived control, we will use postintervention data to assess candidate mediators and 9-month follow-up data to assess depressive symptoms. In each model, the predictor variable will be intervention condition (in Model 1, VR versus Web-based GM intervention; in Model 2, VR versus Web-based ST; and in Model 3, Web-based GM versus Web-based ST); the simultaneous mediator variables will be postintervention perceived behavioral control and postintervention perceived emotional control. We will use bias-corrected bootstrapping to test the significance of specific and total indirect effects within the mediation model. Bootstrapping has the advantage of high statistical power without assuming multivariate normality in sampling distributions, enabling parsimonious analysis of one or several candidate mediators [44,45]. The Iavaan package version 0.5-16 in R version 2.15.1, which is capable of testing both multiple and single mediator models using FIML estimation, will be used for mediation tests [46]. To test for indirect effects of candidate mediators, parameter estimates of total and specific indirect effects are generated, along with their CI, using 1000 to 20,000 random bootstrapped samples. We will specify 5000 resamples in this study per Preacher and Hayes’ [32] recommendations. If the 95% bias-corrected CI for a total indirect parameter estimate does not contain 0, then that indirect effect can be considered statistically significant, demonstrating mediation [44,45]. Using this approach, this study will be sufficiently powered to detect significant indirect effects in each model (bias-corrected CIs for a 2-mediator model show .80 power for samples of 50 and over .90 for samples of 100 [46,47]).

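### Suicidal-ideation answers need only be read before the family leaves, while allocation runs automatically at the end of the youth's baseline survey, so a serious report may be read only after the programme

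*Protocol article*

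**What the plan says.** All references are to the protocol article.

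- **Allocation.** *Laboratory-Based Study Session* places the random number generator "embedded within the last slide of the Qualtrics survey" that holds the youth's baseline questionnaires. For the two Web-based arms, "randomization to these 2 conditions will occur without experimenter involvement".
- **Check of ideation answers.** The closing paragraphs of *Web-Based Supportive Therapy* say: "Before the youth and parent leave the laboratory, study personnel will inspect the youth and parent questionnaire responses on items inquiring about suicidal ideation".
- **Response.** The same paragraphs say: "If there is any indication of adolescent suicidal ideation during the laboratory session, risk assessments will be conducted by trained study personnel". They add: "In the event of reported, active suicidal ideation or plan, the family will be accompanied to the Psychiatric Emergency Program".
- **Supervision.** *Laboratory-Based Study Session* says: "One member of the study team will remain with the youth for the duration of the session". The parent is on site, with a second team member available.
- **Eligibility.** *Recruitment and Screening* decides eligibility by a parent phone screen. The only suicide-related exclusion is a hospital stay in the past 2 months for a suicide attempt or self-harm. The exclusions are explained thus: "as the interventions being evaluated in this study are not designed for youth with acute medical or psychiatric need".

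**The concern.** The baseline survey is the first point in the described procedures at which the youth's own answers are collected. Allocation follows within that survey, and the programme and post-intervention battery come next. Staff could follow every stated step and still first read a report of active ideation or a plan at the end of the visit.

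The protocol itself treats such a report as a reason to escort the family to emergency psychiatric care. Disclosure is also foreseeable: the sample is selected for elevated depressive symptoms, and the protocol has a procedure ready for it. What is at stake is the timing of the safety response for a few youths. The trial result is not at stake.

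**Working it through.** The protocol gives no figure of its own to reproduce. The check is mainly one of sequence, with a rough size for the possible delay.

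**Step 1: order of events as written**
1. Parent phone screen. No youth answer is stated to be used.
2. Youth baseline questionnaires in Qualtrics.
3. Automatic allocation on the last slide of that survey.
4. Programme, about 30 minutes in each arm.
5. Youth post-intervention battery.
6. Latest time for reading the ideation answers: before the family leaves.

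Nothing in the text ties step 6 to step 3 or step 4. Nothing says that a serious answer holds allocation or stops the programme.

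**Step 2: are the ideation answers given before allocation?** The article does not name the instrument that carries these items. In Table 2, every listed youth questionnaire is given at baseline except the Program Feedback Scale. That scale's nine items are printed in Textbox 1, and none asks about ideation. So if a listed youth instrument carries the items, the youth has answered them before allocation. Only an unlisted instrument given after the programme would defeat this.

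**Step 3: possible delay.** Item counts come from the *Questionnaires* section, and timing from Table 2.

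| Post-intervention youth measure | Items |
|---|---|
| Primary control scale | 24 |
| Secondary control scale | 20 |
| Hopelessness, short form | 4 |
| Loneliness | 20 |
| Implicit personality theories | 3 |
| Attitudes toward therapy | 1 |
| Program feedback | 9 (7 rated, 2 free response) |
| **Total** | **81 (79 rated, 2 free response)** |

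Answering times are assumptions: 5 to 10 seconds per rated item and 1 to 2 minutes per free response.

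- Rated items: 79 × 5 s = 395 s = 6.6 min, to 79 × 10 s = 790 s = 13.2 min.
- Free responses: 2 × 1 = 2 min, to 2 × 2 = 4 min.
- Battery: 6.6 + 2 = 8.6 min, to 13.2 + 4 = 17.2 min.
- With the programme: 30 + 8.6 = 38.6 min, to 30 + 17.2 = 47.2 min.
- Share of a visit of about 120 min: 38.6/120 = 32%, to 47.2/120 = 39%.

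If staff look before allocation, the delay is 0.

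**Step 4: number of youths.** No disclosure rate is given. For scale only, each 1% of the planned 159 is 159 × 0.01 = 1.6 youths.

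**The case against.** The strongest reply is that a deadline is a minimum guarantee. It does not forbid an earlier look, and a condensed article may leave the operating detail to the full procedures approved by the ethics board. The text also has real safeguards. A team member stays with the youth, the parent is close by, any sign of ideation during the session triggers a risk assessment, and no family leaves before the answers are read. The document gives no evidence that the programme would harm such a youth.

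Most of this stands, and it keeps the point small. It does not remove it. The article states both the time of the check and the time of allocation, so this is more than an omitted detail. The session-wide trigger works only once someone notices, and nothing makes anyone read a typed answer before the randomiser runs.

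A reader might infer more than the document supports:

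- **Eligibility breach.** Current ideation is not an exclusion, so allocating such a youth breaks no stated rule.
- **Contradiction.** The remark that the programmes are not meant for acute need explains the listed exclusions. It is not a general bar on youths who report ideation.
- **Bias.** The check has the same timing in every arm, and nothing in the text links it to allocation in a way that would distort the comparison.

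One further objection bears on the remedy. Active ideation or a plan may be established only by the staff assessment, and the item wording is not shown. A survey flag must therefore rest on responses to existing items and cannot stand for the clinical threshold itself.

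**Conclusion.** The point holds as an optional safety improvement. As written, a youth who reports serious ideation at baseline may be allocated, complete the programme and complete the post-intervention battery before the answer is read. The delay would be supervised and on site, and about 39 to 47 minutes on the assumed answering times.

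This rests on two assumptions: that the youth ideation items are in the baseline survey, which Table 2 supports well but does not state, and that staff use the latest time the wording allows. If the items are asked only after the programme, the point falls. The number of youths affected cannot be estimated from the document, and no effect on the trial result is claimed.

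**What to change.** Place an automatic Qualtrics check just before the randomisation slide, triggered by a pre-stated most-severe response on the existing youth ideation item or items.

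- **Flagged:** the survey holds and the existing risk assessment is done. Youths who are cleared go on to the automatic randomiser. Youths escorted to emergency care are not randomised at that visit.
- **Not flagged:** the survey runs straight to the randomiser as now. Masking of the Web arms is unchanged, and these youths have no added clinical contact before the Aim 3 mediators are measured ("the simultaneous mediator variables will be postintervention perceived behavioral control and postintervention perceived emotional control").
- **End of visit:** keep the present check of youth and parent answers. It is still needed for parent reports, for later disclosures and for youths whose baseline response falls below the trigger.

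The cost is one survey rule, one stated response threshold and trained risk personnel reachable at that moment. Flagged youths have a short pause and, if cleared, clinical contact between their baseline and post-intervention measures. That contact comes before allocation, so it is not specific to an arm. A few attendees may not be randomised. A narrow trigger keeps these costs low; a broad one would pause many youths in a sample chosen for depressive symptoms.
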